### Inclusion and Exclusion Criteria

3.2

All colonoscopies conducted at participating hospitals will be included (Table 1), regardless of indications and patient risk factors. Individuals who opt out of having their health data audited will be excluded from the study. The hospital coverage captures approximately 50% of the colonoscopies completed in South Australia, and > 80% of procedures completed in government‐run public hospitals [33].

**TABLE 1 cam471456-tbl-0001:** South Australian public hospitals implementing the integrated nurse and digital surveillance program.

Locality	Hospital network	Included hospitals
Adelaide metropolitan	Southern Adelaide Local Health Network	Flinders Medical Centre Noarlunga Health Services
	Northern Adelaide Local Health Network	Lyell McEwin Hospital Modbury Hospital
	Central Adelaide Local Health Network	The Queen Elizabeth Hospital The Royal Adelaide Hospital
Regional	Riverland Mallee Coorong Local Health Network	Riverland General Hospital
	Eyre and Far North Local Health Network	Port Lincoln Hospital

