### Sample Size and Power

3.11

The stepped‐wedge cluster randomised trial includes five local health networks (cluster) with eight participating hospitals, contributing an average of 1417 colonoscopy episodes per 3‐month period (adjusted for 10% attrition) across seven sequential periods (one baseline and six rollout steps). Assuming an ICC of 0.01, a baseline guideline concordance of 60%, and an expected post‐implementation improvement to 75% (15% absolute increase), the design archives approximately 90% power at a two‐sided *α* = 0.05 under a binomial mixed‐effects model. Power was estimated via simulation (*n* = 1000 iterations per effect size), incorporating cluster and period fixed effects. A power curve (Figure S1) illustrates sensitivity to effect size assumptions, a stepped‐wedge design diagram (Figure S2) depicts the rollout sequence, and a summary of power estimates across effect sizes is presented in Table S3.

For the patient‐reported outcomes, assuming eight hospitals with paired before and after implementation (100 participants per hospital per period, total *N* = 1600), we estimate > 80% power (*α* = 0.05, two‐sided) to detect a small‐to‐moderate standardised mean difference (Cohen's *d* ≈ 0.25–0.30) in EQ‐5D‐5L scores, accounting for within‐cluster correlation (ICC ≤ 0.02) and within‐period correlation of repeated measures (*ρ* ≈ 0.5). This is appropriate for evaluating meaningful changes in patient‐reported measures at the hospital level.

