### Statistical Analyses

3.12

All sites will be allowed a three‐month post‐implementation period of transition before outcome measurement. Temporal confounding will be mitigated through the use of models (e.g., interrupted time series analysis) which adjust for secular trends. Given the stepped‐wedge cluster randomised design, analyses will explicitly include fixed effects for time period and intervention status, and random effects for site (cluster) to account for ICC. With only eight clusters, we will apply the Kenward–Roger correction to adjust standard errors and *p* values are not inflated due to small number of clusters. Data analysis will be conducted using Python (3.11) and R (version 4.4.1).

The percentage of surveillance recommendations that match with Australian guidelines will be calculated from audit data, and the prevalence of individuals lost to follow‐up, prevalence of those with acceptable colonoscopy quality, and incidence rates for advanced neoplasia and adverse events will be summarised using descriptive statistics. All measures will be directly compared to each site's own baseline measures in a paired manner using McNemar's tests for proportions, Wilcoxon and Kruskal–Wallis signed‐rank tests for continuous measures and mixed‐effects Poisson regression for incidence rates. Analyses will be conducted on an intention‐to‐treat basis. A prespecified generalised linear mixed model (GLMM) with a logit link will be used for the primary binary outcome (guideline concordance) including fixed effects for time period and intervention, random intercepts for clusters and adjustment for potential confounders (e.g., age, indication and baseline quality metrics). To address the small number of clusters (*K* = 5), we specify that inference will be based on cluster‐preserving parametric bootstrap for both the intervention coefficient and marginal contrasts. Multiple comparisons across secondary outcomes will be controlled using Holm–Bonferroni correction to limit type I error. Additional sensitivity analyses will include (i) cluster‐level summaries with Kenward–Roger correction, (ii) generalised estimating equations with small‐sample corrected SEs and (iii) permutation tests at the cluster level. If national guideline text changes during the trial, an indicator for the new guideline will be included, and analyses will be repeated using both old and new mapping.

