Where relevant, univariate followed by multivariable modelling will be undertaken by adding variables considered clinically important or statistically significant from the univariate model to adjust for confounding effects. Hospitals will be treated as random effects, and main effects will be the intervention group; that is, before and after implementation of the intervention. Missing data will be handled using multiple imputation under the missing‐at‐random assumption. For bowel preparation quality, missing values will be imputed as ‘adequate’ in the primary analysis, reflecting routine clinical documentation where poor preparation is explicitly noted, with sensitivity analyses applying conservative rules assumption imputing missing values as ‘poor’.

Multivariable generalised linear models and pairwise comparisons will be used to assess the association between patient‐reported measures (such as satisfaction with the colonoscopy experience) and acceptance of the digital healthcare approach. Thematic analysis will be conducted to establish clinical end‐user opinions on the surveillance program. Prespecified subgroup analyses will assess intervention effects across patient age, sex, socioeconomic status (by postcode linkage) and hospital location, with multiplicity controlled via Holm–Bonferroni correction. To ensure equitable healthcare delivery, analyses will include age groups ≥ 75 years, comorbidity burden (based on the Charlson Comorbidity Index categories), socioeconomic status and regional vs. metropolitan location.

Quality of life measures will be used to calculate the incremental costs before and after implementation of the intervention per quality‐adjusted life‐year gained (QALY) in a model‐based economic evaluation. Implementation costs will be obtained from administrative data. The economic evaluation will adopt a health‐system perspective with a 12‐month time horizon, 5% annual discounting and QALY derivation from EQ‐5D‐5L value sets. Probabilistic sensitivity analyses will assess parameter uncertainty, and reporting will align with CHEERS 2022 guidelines [43]. Patients will be recruited consecutively at each site, with reminders and follow‐up strategies implemented to maximise retention. Missing responses in surveys and quality‐of‐life instruments will be addressed using multiple imputation under the missing‐at‐random assumption, consistent with the approach for clinical outcomes.

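### The regional-versus-metropolitan subgroup contrast rests on two networks against three, but is listed beside patient-level subgroups with no stated allowance for the intervention effect varying between networks

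*Protocol article*

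**What the plan says.** - Statistical Analyses prespecifies the subgroups: "Prespecified subgroup analyses will assess intervention effects across patient age, sex, socioeconomic status (by postcode linkage) and hospital location". Holm–Bonferroni is the stated multiplicity control. The next sentence, on equitable delivery, lists "socioeconomic status and regional vs. metropolitan location" again, with older age and comorbidity.
- Table 1 (Inclusion and Exclusion Criteria) places three networks in metropolitan Adelaide: "Southern Adelaide Local Health Network", "Northern Adelaide Local Health Network" and the Central Adelaide network, each with two hospitals. Two networks are regional: "Riverland Mallee Coorong Local Health Network" and "Eyre and Far North Local Health Network", each with one hospital.
- Sample Size and Power says the trial "includes five local health networks (cluster) with eight participating hospitals". Implementation is by network.
- The prespecified model for guideline concordance is a logit GLMM with fixed period and intervention effects, "random intercepts for clusters and adjustment for potential confounders". With five clusters, inference is by parametric bootstrap for the intervention coefficient and marginal contrasts.
- Cluster-level summaries with Kenward–Roger, GEE with small-sample standard errors and cluster-level permutation tests are listed as sensitivity analyses. None is tied to the subgroups.
- No model is stated for the subgroup analyses.

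**The concern.** A subgroup factor that varies between patients in the same network can be compared within networks, and a large number of episodes helps. Location is fixed for each network, and so is the date of crossover. Whether the intervention works differently in regional sites is therefore judged by comparing two network-specific effects with three. More episodes per network sharpen each of the five effects but do not add a sixth.

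A random intercept absorbs differences in level between networks. It does not absorb differences in how much each network gains. If the gain varies for reasons unrelated to location, a location-by-intervention term in a random-intercept model attributes that variation to location and gives it too small a standard error. Holm–Bonferroni adjusts for the number of tests, not for a p-value that is already too small. A bootstrap from the same model generates data without the missing variation.

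Equitable service across sites is a stated aim, so a spurious regional difference, favourable or not, would be a consequential finding.

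**Working it through.** **The plan's own figure.** There is none for this contrast. The stated power of about 90% concerns the overall intervention effect and is not used here.

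**Inputs from the article.** Five networks, two of them regional; seven periods; concordance 60% rising to 75%; ICC 0.01; 1417 episodes per 3-month period. The text leaves open whether 1417 is per network or in total, so both are used: 1417, or 1417/5 = 283 per network-period. The Baseline Site Assessments section audits 10% of colonoscopies, and concordance is calculated from audit data, which gives 142 or 28.

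**Assumptions.** Networks of equal size; no true location difference; the primary GLMM carried over with location and location-by-intervention terms; between-network SD of the intervention effect (τ, logit scale) of 0, 0.1 or 0.2. At 75% concordance one logit is 0.75 × 0.25 = 0.1875, so τ = 0.1 is about 1.9 points and τ = 0.2 about 3.7 points.

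**Why the error inflates.** Let s be the standard error that the random-intercept model gives the interaction. The actual SD of the estimate is approximately

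SD = √[s² + τ²(1/2 + 1/3)].

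The model rejects when |estimate| > 1.96 s, so the false-positive rate is P(|Z| > 1.96 s/SD). Simulated s is 0.047, 0.105, 0.147 and 0.325 for 1417, 283, 142 and 28 episodes.

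Worked example, 1417 and τ = 0.2: SD = √(0.0022 + 0.0333) = 0.189; 1.96 × 0.047/0.189 = 0.49; P(|Z| > 0.49) = 62%.

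False-positive rate at nominal 5%, seven-period simulation, with the formula value in brackets:

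| Episodes per network-period | τ = 0 | τ = 0.1 | τ = 0.2 |
|---|---|---|---|
| 1417 | about 5% | 37–40% (37%) | 64% (62%) |
| 283 | about 5% | 14% (14%) | 34% (33%) |
| 142 | about 5% | 10–11% (10%) | 23% (22%) |
| 28 | about 4% | 5–7% (6%) | 8–10% (9%) |

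**Holm–Bonferroni.** If there are four tests, the first step is 0.05/4 = 0.0125 (z = 2.498). At τ = 0.2 the rejection rate is about 55%, 23%, 12% and 3% for the four sizes. The target is 1.25%.

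**Parametric bootstrap from the random-intercept model.** At τ = 0.2 it rejects in 66% (1417) and 34% (283) of null trials; at τ = 0, 4% in both. It does not repair the fault.

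**Network-level alternative.** A t-test with 3 df on the five network-specific effects has a false-positive rate of 4–6% for τ from 0 to 0.3 at 1417, 283 and 142 episodes. For a true location difference of 0.5 logit (about 9 points) with τ = 0.2, its power is 44%, 36% and 32% at 0.05, and 17%, 13% and 10% at 0.0125.

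**Exact permutation of location labels.** C(5,2) = 10 arrangements, so the smallest possible p is 1/10 = 0.10.

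**The case against.** The strongest reply is that the article does not specify the test being criticised. It names location as a subgroup and gives no model; the random-intercept GLMM is prespecified for the primary outcome, and a subgroup model is something an article may leave to a separate analysis plan. That stands, so the error rates above apply only if the primary model is carried over. What the article does fix is the location analysis as one of a Holm-controlled set with patient-level factors, and a primary model unsuited to it.

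It is also fair to say that cluster-level methods are in the plan. A reader might infer that the GLMM is the only model specified; it is not. But the others are sensitivity analyses, not attached to the subgroups.

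The rates also depend on a heterogeneity the documents do not quantify. This stands too. Differences in starting practice alone are absorbed by the random intercepts; only differences in gain, or network-specific drift over time, do harm. With audit samples near 28 per network-period the inflation is small.

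Finally, keeping a prespecified equity subgroup with a suitable network-level model is a defensible alternative to making it descriptive. The fix allows for it.

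**Conclusion.** The point holds in conditional form. Location is a network-level factor with 3 df, listed as though it were a patient-level one. If the primary random-intercept model is used for it, the test is anticonservative whenever the effect varies between networks, and neither stated safeguard corrects that. For an assumed SD of 0.1 to 0.2 logit, the false-positive rate runs from 37–40% up to 64% at 1417 episodes per network-period, and from 5–7% up to 8–10% at 28. These figures assume equal networks, seven periods and no true location difference.

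Two stronger readings are not supported. A reader might infer that chance differences between networks will be declared location effects; the documents give no heterogeneity figure, and with none the error stays near 5%. A reader might also infer that no valid network-level test can reach 0.05; that is true of exact permutation of the location labels only. A 3-df t-test can reach 0.05, but with low power.

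**What to change.** Take hospital location out of the Holm–Bonferroni family. Report the five network-specific intervention effects with confidence intervals, and give the regional and metropolitan averages descriptively. Leave age and sex as within-network interactions.

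If a location test is kept, base it on network-level effects with 3 df, or on a model with a random intervention-by-network effect. State that its power is low and that an exact permutation of location labels cannot give p below 0.10.

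This changes wording only; no data collection is affected. The cost is that a firm significance claim on regional versus metropolitan effect becomes unlikely. The remaining subgroup tests would carry a lighter Holm penalty: with four factors, the first step moves from 0.05/4 = 0.0125 to 0.05/3 = 0.0167.

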## Discussion

4

Best practice guidelines on how frequently surveillance colonoscopy should be performed often have poor adherence [15, 16, 18, 19, 20, 21]. The increasing demand on colonoscopy services [9] lengthens waiting times, thereby increasing patient anxiety, and increasing the risk for CRC and mortality [44, 45]. There is a clear need for a reliable, efficient surveillance program to deliver timely, evidence‐based recommendations for individuals at elevated CRC risk.

This study will evaluate the integration of a digital, algorithm‐supported approach into a nurse‐led surveillance program. By reducing inappropriate procedures [15, 16, 17], this model has the potential to improve cost‐effectiveness and reduce burdens on primary and specialist care. Importantly, it also aims to address under‐servicing of high‐risk individuals.

Although the study is limited to five hospital networks in South Australia, these sites represent a mix of metropolitan and regional centers and cover over 80% of public colonoscopies in the state [33]. This focused implementation enables robust evaluation before potential national or international scale‐up. In addition, this study's strength lies in the integration within the framework of the nurse‐coordinated SCOOP surveillance program to maximise clinical efficiency. The stepped‐wedge trial design ensures practical rollout across sites. As the SCOPES program is tailored to Australian healthcare settings and guideline frameworks, further work will be needed to evaluate adaptability across international health systems and contexts before broader implementation.

## Conclusion

5

This study will implement a digital, nurse‐coordinated model to automate data collection and streamline surveillance colonoscopy recommendations, ensuring that all patients receive evidence‐based care, and improving CRC prevention. By capturing patient‐reported outcomes and collecting high‐quality clinical data, the program also provides a platform for continuous improvement in surveillance practices.

## Ethics Statement

This study was approved by the Southern Adelaide Clinical Human Research Ethics Committee (SAC HREC), Adelaide, South Australia (HREC approval number 2024/HRE00165). SCOPES (Surveillance for Colorectal Cancer Prevention) is registered with the Australian New Zealand Clinical Trials Registry (number: ACTRN12624001429549, registered 6 December 2024).

## Data Availability

De‐identified registry extracts and analytic code will be made available upon reasonable request, following governance approval and institutional data‐sharing policies. Please contact the corresponding author for further details.

